## Abstract

**Background:**

Acquired Brain Injury (ABI) admissions have an incidence of 385 per 100,000 of the population in the UK, and as brain injury often involves the frontal networks, cognitive domains affected are likely to be executive control, working memory, and problem-solving deficits, resulting in difficulty with everyday activities. The above observations make working memory, and related constructs such as attention and executive functioning attractive targets for neurorehabilitation. We propose a combined home-based rehabilitation protocol involving the concurrent administration of a working memory training program (adaptive N-back task) with non-invasive transcranial direct current stimulation (tDCS) of the right dorsolateral prefrontal cortex to promote long-lasting modification of brain areas underlying working memory function.

**Method:**

Patients with a working memory deficit will be recruited and assigned to two age-matched groups receiving working memory training for 2 weeks: an active group, receiving tDCS (2 mA for 20 min), and a control group, receiving sham stimulation. After the end of the first 2 weeks, both groups will continue the working memory training for three more weeks. Outcome measures will be recorded at timepoints throughout the intervention, including baseline, after the 2 weeks of stimulation, at the end of the working memory training regimen and 1 month after the completion of the training.

**Discussion:**

The aim of the study is to assess if non-invasive tDCS stimulation has an impact on performance and benefits of a working memory training regimen. Specifically, we will examine the impact of brain stimulation on training gains, if changes in gains would last, and whether changes in training performance transfer to other cognitive domains. Furthermore, we will explore whether training improvements impact on everyday life activities and how the home-based training regimen is received by participants, with the view to develop an effective home healthcare tool that could enhance working memory and daily functioning.

**Trial registration:**

This study was registered with clinicaltrials.gov: NCT04010149 on July 8, 2019.

## Background

Working memory, which involves temporary maintenance and working with information in mind, is required for cognitive skills such as problem solving, planning and auditory and reading comprehension. Working memory operates across multiple modalities (e.g., auditory and visual), and is a system that combines attentional control with temporary storage and information manipulation [1]. A core concept of Baddeley’s [2] model of working memory is that it consists of multiple components: namely, a phonological loop governing for temporary maintenance and processing of verbal information, a visuospatial sketchpad to maintain and process visual and spatial information, an episodic buffer that bridges working memory and long-term memory, and a central executive that exercises attentional control over the above-named subsystems. A network involving the dorsolateral prefrontal cortex (DLPFC) plays a fundamental role in supporting working memory [3], with spatial tasks primarily involving the right DLPFC and verbal task involving the left DLPFC [4, 5].

Working memory is important for everyday tasks such as problem solving, reasoning, and learning [1] ; a deficit in working memory can lead to difficulties with many everyday activities that are necessary for work, study and general functioning [6]. Impaired working memory may consequently have a significant impact on quality of life and ability to participate in social roles, with potential for negative effects on mood and emotional wellbeing. Working memory is known to decline with aging [7] and is frequently compromised following brain injury [8].

Acquired Brain Injury (ABI) is brain damage caused by either a traumatic (e.g. a penetrating head injury due to an accident) or a non-traumatic injury (e.g., stroke, brain tumours, ischemia). ABI may be associated not only with physical but also with cognitive, emotional and behavioural impairments. Our research focuses on cognitive impairment resulting from ABI. As brain injury often involves frontal systems, cognitive domains commonly affected include: attention, executive control, working memory, and problem solving [9, 10]. Working memory impairment is highly prevalent across ABI aetiologies [11, 12] and severity levels. A recent meta-analysis of working memory deficits post traumatic brain injury revealed significant deficits in verbal short-term memory and visuospatial and verbal working memory (effect sizes ranging from .37 to .69 [11];).

The above observations make working memory, and overlapping constructs such as attention and executive functioning, important targets for neurorehabilitation, given the impact of these deficits on everyday function [6, 13]. Admissions for ABI have an incidence of 385 per 100,000 in the UK (https://www.headway.org.uk/about-brain-injury/further-information/statistics/). Individuals post ABI commonly report working memory dysfunctions [14, 15], thus solutions to improve recovery of working memory are critically needed.

Researchers have been exploring whether it is possible to train or improve working memory in clinical groups such as stroke patients [16], people with Parkinson’s disease [17], and children with attention deficit hyperactivity disorder (ADHD) [18]. For training to be considered of value, the gains in performance on the training task must transfer to other cognitive tasks or yield some benefit in daily function outside of the laboratory [19]. However, evidence for transfer to other cognitive tasks or daily activities is not yet consistently obtained [20].

Rehabilitation for working memory impairments can focus on compensatory strategies, which aim to compensate for the impaired functions by using those which remain intact, or supplementary external aids [21]. In contrast, recent studies have focused on increasing working memory capacity through extensive practice and training [19, 22]. Computerized working memory training has shown promising results in healthy participants [23, 24] as well as in ABI patients [7, 16, 25–27]. Mood measures also appear to improve following working memory training [21, 25]. One of the tools that has been assessed for its working memory training potential is the n-back task, which involves determining whether a new item in a sequence is the same as the one that appeared ‘n’ times before. While results have been mixed (likely due in part to methodological inconsistencies between studies [28], a dual n-back implementation wherein participants keep track of two streams of information (one audio and one visual), was successful in healthy participants [23, 24].

Brain plasticity, which can vary greatly by individual, plays a central role in the success of cognitive training. Transcranial direct current stimulation (tDCS) [29–32] is a non-invasive technique that is thought to modify cortical excitability which, in turn, can directly affect brain plasticity by making relevant brain networks more or less likely to fire synchronously. Synchronous firing has been suggested to modulate long-term potentiation (LTP) like plasticity at the synaptic level, a critical component for learning [33, 34].

The combination of cognitive training protocols and non-invasive tDCS has gained attention as a means for cognitive enhancement in both adults and older adults [35–37]. In young and healthy participants, anodal tDCS over the left or right dorsolateral pre-frontal cortex (DLPFC) improved working memory when administered concurrently with cognitive training using a n-back task, also showing transfer to other domains [38], as well as maintenance over time [39]. Preliminary evidence shows that the congruency between the side of stimulation, and therefore the functional specificity of the DLPFC, and the behavioural task plays an important role in training outcome [40, 41]. As many cognitive functions show a physiological decline even in healthy aging, combined tDCS/cognitive training protocols are of particular interest for older adults [37, 42, 43] but in the elderly results are mixed with some studies revealing null findings [35, 44, 45].

Despite encouraging results obtained in healthy populations, research involving brain stimulation in ABI patients is sparse. By stimulating over the left DLPFC, Kang et al. [46] obtained positive results on attention, albeit in a small sample. In a within-subject design, working memory performance in stroke patients can improve after anodal stimulation of the left DLPFC [47]. Villamar et al. [48] reviewed the potential of the therapeutic use of brain stimulation to modulate neuroplasticity in ABI patients; however, given the diversity of the nature of the lesions, more research is necessary to understand how to use brain stimulation effectively in ABI populations.

## Aims and objectives

The aim of this research project is to investigate the impact of combined working memory training and tDCS protocols in individuals following a brain injury in terms of the training gains, change in objective measures of working memory, mood and fatigue, as well as participants’ perceptions of day-to-day memory function and subjective benefit of the training program.

Specifically, our primary objective is to determine if the combination of tDCS and working memory training is superior to working memory training alone to improve working memory function in an n-back task in an ABI population. The key secondary objectives are to determine if the combination of brain stimulation with working memory training can:
boost performance in other cognitive domains (attention, executive functions)speed training gainslengthen improvement duration to 1 monthincrease improvement magnitude

To address the above questions, we will use a randomized clinical trial, assessor- and patient-blinded with two parallel groups and a simple randomization with a 1:1 allocation ratio.

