##### Baseline session

After the informed consent process is carried out, eligible participants are administered the baseline measures (T0). The baseline data are included in data analyses as potential modifiers of performance. The baseline measures involve completing a series of questionnaires (Table 5). On the same day of baseline testing, patients are given a diary for them to keep. The diary contains information on how to setup and use the training program on their computer, education on how to do the working memory training, general troubleshooting information, and also a daily table to record information about the training session and any issue they might experience. The diary also contains contact details of the researcher administering the stimulation and information about future appointments. In addition, participants are asked to refrain from excessive alcohol or caffeine intake during the testing and to maintain good sleeping habits, where possible. In total, we expect the entirety of the first in-lab session (informed consent, screening, and baseline measures (T0)) to take about 1 h.

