#### Cognitive tasks and questionnaires

A series of cognitive tasks will be administered at different time points and for a different purpose during the study: *screening*, *training*, and *outcome assessment*.
Screening: the Digit Span, Arithmetic, Symbol Span, and Spatial Addition subtests from the WAIS-IV and WMS-IV will be used for screening participants for cognitive impairment (see 3.5.4, 35 min to complete). A description of the task is given in Table 3.Training Task: The visuo-spatial training task is a visuo-spatial adaptive n-back (see section 3.5.3).Outcome: 1) the Dalhousie Computerized Attention Battery (DalCAB, [68], 35 min to complete) will be used as the outcome assessment battery. A description of the tasks in the battery is provided in Table 4. For a detailed description of the parameters used in each task see [68]; 2) In addition, a non-adaptive visuo-spatial N-back task will also be used as outcome measure, with fixed levels of *N* = 1,2,3. (~ 30 min to complete); 3) The Digit span, Arithmetic span, Symbol span and spatial addition will also be used as outcome measures.A series of questionnaires and feedback forms will also be administered at single or multiple time points throughout the intervention to record variables that may impact or may be affected by performance on the task. Permission to use these instruments has been obtained for those questionnaires requiring it. A list of the questionnaires, together with a brief explanation and references is presented in Table 5.

**Table 5 Tab5:** Questionnaires

	Questionnaire	Taken at
*Individual lifestyle*	Participant Health History (including details on injury, medications etc..)	T1
	Epworth Sleepiness Scale (to report habitual sleepiness [62]	
	Quality of life assessment (The Whoqol Group [63]), − in four facets (Physical health, Psychological, Social relationships, Environment)	
*Individual cognitive state*	Cognitive Failures Questionnaire (CFQ, [64]) to measure self-reported failures in perception, memory, and motor function.	T1
	Hospital Anxiety and Depression Scale (HADS) to measure emotional symptoms (HADS; [65])	
	Patient Reported Evaluation of Cognitive Status (PRECiS [66];)	T1/T3/T4
*Feedback on the of intervention*	Side effect of the tCS [57]	Every tCS session
	System usability scale (SUS [67];)	T3
	Attitude towards stimulation (to record how they feel their attitude towards the brain stimulation affected performance)	

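### Change in mood and fatigue is part of the general aim, but on the visible schedule the mood scale is taken only before training and no fatigue scale is listed

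*Protocol article*

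**What the plan says.** The opening sentence of Aims and objectives lists what the trial will study. Alongside training gains and patients' own view of their memory, it names "change in objective measures of working memory, mood and fatigue". The next paragraph sets the primary objective (n-back performance) and the key secondary objectives (other cognitive domains, and the speed, duration and size of improvement). Mood and fatigue are in neither list.

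Table 5, under Cognitive tasks and questionnaires, gives the questionnaires and when they are taken:

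- Mood: "Hospital Anxiety and Depression Scale (HADS) to measure emotional symptoms". Its own timing cell is blank in the text at hand. It follows the row "Cognitive Failures Questionnaire (CFQ, [64]) to measure self-reported failures in perception, memory, and motor function", which is marked T1.
- PRECiS, the next row, is marked T1/T3/T4.
- Nearest to fatigue: "Epworth Sleepiness Scale (to report habitual sleepiness", in the first block, also marked T1.
- The side-effect form is marked for every stimulation session.

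The Baseline session section says of the data collected there: "The baseline data are included in data analyses as potential modifiers of performance". Under Training phase 1, patients also answer a few questions on alertness and engagement before each session and complete a side-effect form afterwards.

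**The concern.** To estimate the effect of stimulation on mood or fatigue, the trial needs at least one measurement of each, in both groups, after treatment has begun. If the only mood measurement precedes training, any difference between groups on it is chance, because nobody has yet been stimulated. If no fatigue scale is listed, that part of the aim has no defined endpoint.

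This differs from a detail that an analysis plan can supply later. An analysis plan can choose a model for data that exist, but it cannot recover a questionnaire that was never given. What is at stake is whether the trial can report on two elements of its stated aim.

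**Working it through.** No figure in the plan needs to be reproduced. The check sets the aim beside each part of the protocol article that could supply a measurement.

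**1. Timing of HADS.** Table 5 appears to use merged timing cells: one entry covers the rows below it until the next entry. Epworth and quality of life then fall under the T1 entry for health history, HADS under the T1 entry for the cognitive failures questionnaire, and the attitude and strategy forms under the T3 entry for the usability scale. On that reading HADS is taken at T1. Where repetition was intended, the table says so, as for PRECiS and the side-effect form.

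**2. Count by assessment.**

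| Construct in the aim | Instrument | T1 | T2 | T3 | T4 |
|---|---|---|---|---|---|
| Mood | HADS | yes | none listed | none listed | none listed |
| Fatigue | no dedicated scale | none | none | none | none |
| For comparison: self-rated cognition | PRECiS | yes | none listed | yes | yes |

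HADS: 1 pre-training measurement, 0 of 3 later ones. Dedicated fatigue scale: 0 of 4. The Baseline session section places the baseline questionnaires at T0, where Table 5 has T1. Both precede training, so the count of later measurements does not change.

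**3. Visit descriptions.** The sections on T2, T3 and T4 describe cognitive testing. None mentions a mood or fatigue scale.

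**4. Outcome measures section.** It lists training gain, transfer, maintenance and everyday-life improvement. PRECiS is the only self-report outcome; mood and fatigue do not appear.

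**5. Other possible sources.**
- The alertness and engagement questions and the side-effect form cover up to 10 sessions per patient, in both groups, during the two stimulation weeks. No T3 or T4 collection is stated, and neither is named as an outcome.
- Risk assessment and monitoring mentions fatigue only as a common side effect of tDCS.
- The quality-of-life scale has a psychological facet but falls in a T1 block.

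**6. Consequence.** With HADS at T1 alone, there is no change score, no baseline-adjusted comparison and no simple post-training comparison. For fatigue, at most tolerability-type records exist during stimulation, with nothing defined at the assessment visits.

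**The case against.** The strongest reply is that the deciding page is missing. Table 2, the schedule of assessments, is not shown, and neither is the flowchart; a later HADS could be there. The blank timing cell for HADS means that T1 is inferred from layout, and tables in this text may be broken. The article also says in general terms that questionnaires are given at one or several time points. This stands as a limit on certainty. It does not remove the point: the visible Table 2 footnotes name only cognitive tests and training gains (though they do not rule out questionnaire rows), and a later HADS in Table 2 would conflict with Table 5 as read here.

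A second reply is that fatigue is not wholly unrecorded. This also stands. A reader might infer that the trial will hold no fatigue data at all, but the documents do not support that: the per-session records exist, and the items on the side-effect form are not shown. What they lack is a stated T3 or T4 collection and the status of an outcome.

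Third, the statement that baseline data serve as modifiers does not prove that HADS is baseline-only. PRECiS is in the same table, is taken at T1 and is also an outcome. That sentence carries little weight either way.

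Fourth, the consequence is limited. No primary or key secondary objective, named outcome or sample size figure depends on mood or fatigue.

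**Conclusion.** The point holds as a mismatch between the general aim and the visible measurement schedule. As scheduled, a between-group effect on mood cannot be estimated, and fatigue has no outcome measure at the assessment visits. The assumptions are that the blank HADS cell takes the T1 entry above it and that Table 2 does not add a later HADS.

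Its reach is modest: two elements of a general aim, outside the primary and key secondary objectives. It merits correction because it is cheap to correct before data are collected and cannot be repaired afterwards.

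Two wider readings are not supported. One is that the single measurement of sleepiness, quality of life or cognitive failures is itself a defect. Sleepiness and quality of life are not in the aim, and self-perceived memory function already has a repeated measure in PRECiS. The other is that silence on mood and fatigue would be taken as no effect; nothing in the documents bears on that. The T0/T1 labelling difference is a separate editorial matter.

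**What to change.** For mood, add HADS at T3 and T4 beside PRECiS, list it among the outcomes, and compare groups at each visit adjusted for the T1 score. For fatigue, either schedule a brief self-report fatigue measure at T1, T3 and T4 and list it likewise, or delete fatigue from the aim. If no repeat of either is wanted, delete both terms from the opening sentence of Aims and objectives. In every case make Table 2 and Table 5 agree, with an explicit time point in each questionnaire row.

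Repeating HADS costs a few minutes of self-completed forms at two existing visits; a fatigue measure would add a short form at three. The alternative costs one deleted phrase.

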## Methods/design

### Study setting

Patients will be recruited from the Northamptonshire Healthcare NHS Foundation Trust (NHFT) by the Community Brain Injury Service, a multidisciplinary service that provides specialist neurorehabilitation to adults who have experienced an acquired brain injury. People accessing the service from which the participants will be recruited are aged 16 and over; the most common age group from an audit of last year’s referrals was 50–59, with the majority falling between the ages of 30–69. Aetiology of brain injury varies although traumatic brain injury accounted for over half of referrals last year, followed by stroke, tumours and then hypoxia and infection related ABI. The ratio of males to females was 60:40.

Training sessions with brain stimulation will be administered at home by a member of the research team (assessor), who will visit the patient at an agreed time for the first 2 weeks. During the remaining 3 weeks, patients will complete the cognitive training alone from home, via an internet-based application, while receiving a motivational catch up call every week. Weekends will be exempt from training. This home-based approach will help us reduce drop-out. Moreover, it will also increase convenience for the patient, many of whom may live some distance from the brain injury team base.

### Eligibility criteria

The study will recruit patients who experienced an ABI and have been referred to the Community Brian Injury Service of NHFT. Patients provide written, informed consent before any study procedure occurs (see Fig. 2) and must meet eligibility criteria (Table 1) at randomization. Assessors, who will also administer the brain stimulation, will receive training in the use of tDCS and basic life support.

**Table 1 Tab1:** Eligibility criteria

**Inclusion Criteria**	
1. Referred to the service 2. Are between 18 and 69 years of age, inclusive 3. Have capacity and able to provide informed consent 4. Normal or corrected-to-normal vision and hearing 5. Having a working memory impairment (see screening procedure) 6. At least 3 months between the injury and the starting of the study 7. Has a computer or has access to a computer	
**Exclusion criteria**	
1. Pre-injury psychiatric or neurological disease by self-report (e.g., anxiety disorder, ADHD, Parkinson’s disease, etc.) 2. History of diagnosed severe depression (diagnosed pre-injury) 3. History of epilepsy (diagnosed pre-injury) 4. Family history of epilepsy 5. Have had fainting spells or syncope in the last 3 years pre-injury 6. Have significant hearing loss, vision or motor impairment that would prevent them from performing the task 7. Known to be pregnant 8. Consuming medication affecting cortical excitability or recreational drugs^a^ 9. Metal (except titanium) or electronic implants in the brain /skull (e.g., splinters, fragments, clips, cochlear implant, deep brain stimulation, medication pump…) 10. Metal (except titanium) or any electronic device at other sites in your body, such as cardiac pacemaker or traumatic metallic residual fragments 11. Have skin problems such as dermatitis, psoriasis or eczema under the stimulation sites 12. Have had brain stimulation in the past 6 months 13. Have undergone transcranial electric or magnetic stimulation in the past (more than 6 months) which resulted in adverse effects 14. Skull fractures, significant skull defects, skull plates or large vessels occlusions, no significant cortical lesion or atrophy at the site of electrode 15. Having had a seizure at the time of accident or between the injury and starting of the therapy.	

^a^We follow recommendations by McLaren et al. [49], and only exclude drugs that are shown to block tDCS effects (e.g., sodium channel blockers, calcium channel blockers, and NMDA receptor antagonist), while other medications shown to only modulate tDCS effects will be tracked and considered as covariate in the analysis. We will monitor for medication changes as a potential bias on the outcomes of the intervention and report any changes that may occur. If a patient become in need of medications shown to block tDCS effects, they will be excluded from further participation. We will monitor changes in medication and general health through in-person briefing during the first 2 weeks of the intervention, when a researcher is visiting the patient’s house, and via phone calls (e.g. “Have there been any changes in your health or medications since our last phone call?”) during the remaining 3 weeks of the intervention

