### Recruitment

Forty adults between the age of 18 and 69 years will be recruited through the Community Brain Injury Service. Patients will be randomly assigned to one of two experimental groups: an active (or right-sided tDCS) group and a control (or SHAM) group. All patients will receive WM training. As there is evidence that age modulates individual responses to both tDCS [50–52] and training regimens [53, 54], the two groups will be age-matched in two age subgroups: those aged between 18 and 45 years and those aged between 46 and 69 years, randomised within age range. Other factors may also influence the impact of the intervention on patients, including medications, time since injury, baseline performance, and these factors will be included as regressors in the analysis whenever appropriate. To reduce the variability due to different locations of lesions, patients with lesions underneath the electrodes (that could modify the induced electric field) will be excluded. Finally, as explained in the following, patients will only be included if they present with a working memory deficit, but no general intellectual impairment.

As the aim of this research is to improve working memory, only participants with a working memory impairment will be included. As we are focusing on improving a documented working memory deficit, we will not attempt to distinguish between pathologies (unless otherwise determined by the exclusion criteria for tDCS, e.g. a lesion underneath the electrodes), rather we will screen patients based on working memory performance. Final analysis will explore differences between pathologies. To identify a working memory impairment, cognitive tests from the Wechsler Adult Intelligence Test (WAIS-IV) and the Wechsler Memory Scale (WMS-IV) will be administered. These tests are administered to every patient as part of the routine care protocol. We will use the following scores:

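### The last clause of exclusion criterion 14 in Table 1 runs in the reverse direction and contradicts the Recruitment section on lesions under the electrodes

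*Protocol article*

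**What the plan says.** Table 1 of the protocol article has an inclusion list and a list headed "Exclusion criteria". Item 14 of the second list has two parts. The first names skull and vessel conditions: "Skull fractures, significant skull defects, skull plates or large vessels occlusions". The second, in the same sentence, is "no significant cortical lesion or atrophy at the site of electrode".

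The Recruitment section deals with the same matter in two places. It opens one sentence with the purpose, "To reduce the variability due to different locations of lesions", and goes on to say that "patients with lesions underneath the electrodes (that could modify the induced electric field) will be excluded". A paragraph later it explains that pathologies will not be distinguished, "unless otherwise determined by the exclusion criteria for tDCS, e.g. a lesion underneath the electrodes".

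The Eligibility criteria section sets the status of the table: patients "must meet eligibility criteria (Table 1) at randomization". The Participants' timeline section says that the assessor evaluates the inclusion and exclusion criteria with a screening questionnaire at the first session. That questionnaire is not shown.

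**The concern.** An exclusion list is read in one direction: a patient who has the listed feature is out. The final clause of item 14 lists the absence of a feature. Read literally, it removes patients without a lesion or atrophy at the electrode site and says nothing against those who have one. That is the reverse of the Recruitment section.

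Two things are at stake. The first is consistent enrolment. Staff working from Table 1 and staff working from the Recruitment text would reach opposite decisions on the same patient. The second is the purpose the protocol gives for the exclusion, which is to limit variability from lesion location and to avoid lesions that could alter the induced field. The question is not remote in this trial: the Background says that brain injury often involves frontal systems, and the stimulating electrodes are frontal (F4 and Fp1, Brain stimulation protocol section). A reader of the results would also rely on Table 1 to judge who was eligible.

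**Working it through.** No formula applies and the plan gives no figure to reproduce. The check sets the two rules side by side.

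Inputs:
- Direction of the list: the heading over item 14 in Table 1, "Exclusion criteria".
- Rule A: the last clause of item 14. Literally, exclude if there is neither a significant cortical lesion nor atrophy at the electrode site.
- Rule B: the main Recruitment statement. Exclude if there is a lesion underneath the electrodes.
- Status of Table 1: to be met at randomization (Eligibility criteria section).

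Step 1. Apply both rules to the four possible findings at the electrode site. Here the lesion is taken to be a significant cortical one that could modify the field, so that both rules address it.

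| Finding at the site | Rule A (Table 1, literal) | Rule B (Recruitment) | Both together |
|---|---|---|---|
| No lesion, no atrophy | Excluded | Not excluded | Excluded |
| Lesion, no atrophy | Not excluded | Excluded | Excluded |
| Lesion and atrophy | Not excluded | Excluded | Excluded |
| Atrophy only | Not excluded | Not excluded | Not excluded |

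The rules disagree in three of the four rows. Applied together, they leave only patients with atrophy and no lesion. If the clause is instead parsed as no lesion, or else atrophy, the last row is excluded by Rule A as well and no patient remains. On either parse the two passages cannot both be operated.

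Step 2. Check whether the whole of item 14 is affected. It is not. The skull and vessel conditions are listed by their presence, as an exclusion list requires. Direction changes only at the last clause.

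Step 3. Check which direction the rest of the article supports. Both Recruitment statements make the presence of a lesion the excluding feature. The second, "unless otherwise determined by the exclusion criteria for tDCS, e.g. a lesion underneath the electrodes", refers to the exclusion criteria themselves, so the article describes its own list in the opposite sense to what the list says. No passage argues for excluding patients with intact cortex.

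Step 4. Check whether matching the direction is enough. If the clause were worded by presence, the first three rows would agree. The atrophy-only row would then differ, because Table 1 names atrophy and the Recruitment section does not. A minor or non-cortical lesion could also be classified differently: Table 1 limits the clause to significant cortical lesions, whereas the Recruitment section speaks of lesions, with a parenthesis about the induced field. A difference of scope therefore remains after the direction is settled.

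**The case against.** The strongest reply is that this is a slip and that the intent is plain. The Recruitment section states it twice, nothing defends the literal reading, and a rule that rejects patients for having intact cortex under the electrode would probably be noticed at the first screening. The clause reads like an inclusion-style phrase that landed in the exclusion list. All of this is fair. It lowers the likely harm but does not remove the contradiction, because the slip is in the table that patients must meet and not in background text.

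The reply is also right against several stronger readings that a reader might draw:
- That criterion 14 as a whole is inverted. Only its last clause is.
- That the wording reverses a safety rationale. The article gives variability and the electric field as the reasons for the lesion exclusion. It states no safety reason for it.
- That this clause is the only safeguard against lesions under the electrodes, or the only limit on variability of the field. The Recruitment text is itself a stated exclusion, and nothing shows that the skull-defect and implant items have no bearing on the field.
- That the Recruitment text excludes every lesion of any kind. It does not say so, and its parenthesis about modifying the field can be read as a qualifier close to Table 1's word significant. A narrative paragraph also need not repeat every term of a table. The scope difference is therefore a matter of two wordings that should be made one, and not a second contradiction.

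**Conclusion.** The point holds for the last clause of item 14. As written it contradicts the Recruitment section, and since Table 1 governs eligibility at randomization, the two must be reconciled.

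Its size cannot be put as a number. The documents do not say how many referred patients have a lesion or atrophy at the electrode sites. A reader might infer that the eligibility of all 40 planned patients is compromised, or that patients with lesions under the electrodes will be admitted. The documents support neither. Admission would require staff to apply Table 1 alone, literally and against the Recruitment text, and nothing shown indicates that they would. The supported conclusion is a wrong operative rule with a risk of inconsistent enrolment. No sample size, power or analysis figure depends on it.

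This rests on two assumptions: that the clause is read under the heading it stands beneath, and that the article reproduces the eligibility table of the full protocol. If the full protocol words the clause differently, the correction is needed only in the article.

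**What to change.** Reconcile the last clause of item 14 in Table 1 with the Recruitment section so that both state the same direction. Keep it apart from the skull and vessel items, which need no change of direction.

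Use one wording for scope in both places. The investigators should decide, and state once, whether the rule concerns significant lesions or lesions that could modify the field, whether it is limited to cortical lesions, and whether atrophy is included.

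Then check that the screening questionnaire carries the same wording. It is not shown, so whether it needs correcting is unknown.

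The cost is about one line in the table, a matching phrase in the Recruitment section and a check of one form. No recalculation is needed.
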